## Abstract

**Background:**

The current uptake of many vaccinations recommended for persons aged 60 and older is unsatisfactory in Germany. Lack of confidence in the safety and efficacy of vaccinations, lack of knowledge and insecurities about possible side effects, and numerous pragmatic barriers are just some of the reasons to be mentioned. General practitioners (GPs) play a central role in the vaccination process. Therefore, effective interventions in this context are needed to address the various barriers and improve the vaccination uptake rates.

**Methods:**

A complex intervention will be implemented and evaluated in 1057 GPs’ practices in two German federal states. The components include trainings for GPs and medical assistants on communication psychology, medical aspects, and organisational vaccination processes. The primary outcome influenza vaccination rate and the secondary outcomes vaccination uptake rate of other vaccinations as well as vaccine literacy of patients will be examined. The intervention will be evaluated in a mixed methods study with a controlled design. Survey data will be analysed descriptively and by using mean comparisons as well as multivariable multilevel analyses. The qualitative data will be analysed with qualitative content analysis. The secondary data will be analysed by using descriptive statistics, a pre-post comparison by performing mean comparisons, cluster analysis, and subgroup analyses.

**Discussion:**

In this study, a complex intervention to improve vaccination rates in GP practices for the vaccinations recommended for people aged 60 years and older will be implemented and evaluated. Additionally, improvements in patients’ vaccine-related health literacy and knowledge, and patients’ intention to get vaccinated are expected. The mixed methods design can deliver results that can be used to improve preventive health care for elderly people and to gain more knowledge on vaccination uptake and the intervention’s effectiveness.

**Trial registration:**

Trial registration number: DRKS00027252 (retrospectively registered).

**Supplementary Information:**

The online version contains supplementary material available at 10.1186/s12875-023-02101-w.

## Background

With older age the prevalence of chronic conditions such as diabetes mellitus or cardiovascular problems is increasing. At the same time, the age-associated weakening of the immune system contributes to an increased incidence and severity of infectious diseases. Therefore, severe courses or life-threatening complications from infections occur more frequently with older age [1–4]. Infections such as seasonal influenza can therefore last longer or run a more severe course, with serious health risks such as pneumonia or myocarditis. In addition, the risk of secondary diseases (e.g., sepsis as a result of influenza or pneumococcal infection) is higher in patients aged 60 and older. There is also a significant increase in mortality as well as hospitalization among elderly people infected with influenza [5]. The COVID-19 pandemic also shows the increased vulnerability of people in older age to new pathogens [6, 7]. For these reasons, the uptake of existing vaccinations for patients aged 60 and older is of major relevance for preventing the aforementioned severe consequences.

In Germany, the current uptake of vaccinations that are recommended for this age group according to the Standing Committee on Vaccination (STIKO; seasonal influenza, pneumococci, herpes zoster and revaccinations against tetanus, diphtheria and pertussis) is unsatisfactory [8]. In particular, the annual influenza vaccination rate is low in the age group 60 and older (influenza season 2020/2021: 47.3%) and far from the rate of 75% recommended by the Council of the European Union [8, 9]. The rates for pneumococcal vaccination in Germany are low and vary widely between 14.8% and 40.4% depending on the region in the age group between 60 and 73 years [8]. The vaccination rate against herpes zoster in the German population over 60 years is generally extremely low, in the single digits [8].

The reasons for the rather low vaccination rates in Germany in European and international comparison are multifactorial [10–12]. Numerous studies show that a number of psychological, contextual, sociodemographic, and pragmatic barriers to influenza vaccination uptake exist. Lack of trust, inconvenience, calculation, and complacency are reported to be barriers to influenza vaccination in risk groups to varying degrees [13]. In addition to a lack of trust in the safety and effectiveness of vaccinations and incomplete knowledge about possible side effects [14, 15], a misconception of vulnerability to certain diseases and their effects on health in the elderly is also a significant reason for the low uptake. Furthermore, a low sense of responsibility towards the community as well as a lack of understanding with regard to the necessary herd immunity also have an influence on individual vaccination motivation and uptake. In addition, numerous pragmatic barriers exist on the part of patients and general practitioners (GPs). These are, for example, lack of time, access to GP practices or forgetfulness [13, 16]. In Germany, vaccinations are usually provided by GPs [17]. Studies show that physicians’ recommendations are an important influencing factor that patients are aware of vaccinations [13]. The mentioned diverse reasons for the individual decision to get vaccinated are summarised within the following domains of the 5 C model: confidence, complacency, constraints, calculation, collective responsibility [16, 18]. These domains apply not only to the elderly, but to the general population. Effective measures are needed to address these diverse barriers. For example, effective communication strategies and techniques used by GPs during the encounter can help improve education and counselling and thereby increase patients’ trust in vaccinations and relevant knowledge. Studies show that by using motivational interviewing, emerging concerns and fears can be addressed empathically and precisely [19]. When dealing with vaccination myths and misinformation, it is important to use targeted communication and to address the techniques used, for example, in vaccine-sceptic argumentation [20, 21]. For GPs, it is also important to know the reasons for non-vaccination and to be aware of vaccination fatigue. Structural barriers can be effectively addressed by implementing vaccination recall systems – a procedure that has already achieved positive effects in numerous studies [22, 23]. In this context, medical assistants in GP practices have an essential function. They are the first point of contact for patients and are responsible for administrative practice procedures. It can therefore be important to integrate medical assistants into the vaccination process and, after appropriate training, to give them responsibility for vaccination management [24, 25].

### Description of the complex intervention

Against the aforementioned background, a bundle of measures to increase vaccination uptake will be implemented in GP practices. The aim of the intervention is to raise further awareness among GPs and medical assistants about the importance of vaccinations for patients aged 60 and older, to provide them with training in vaccination expertise and communication psychology, to introduce suitable tools for vaccination recall into their practice routines, and to update them on where to find target group appropriate information for patients.

As the first component of the intervention, GPs and their medical assistants complete an accredited online training. The main goal of the online training is to increase medical knowledge about vaccinations and vaccination counselling skills. This is intended to promote vaccine-related communication between GPs and patients, improve patient vaccine literacy, and thereby increase vaccination uptake. Furthermore, participating GP practices will receive a first material package containing appointment reminder cards, a poster on vaccination, checklists on the vaccination procedure in outpatient care and nursing homes, an infosheet with the most important contents from the online training, an immunisation schedule with an overview of recommended vaccinations, and templates of consent forms for vaccination reminders for the following influenza vaccination season.

In the second year of the intervention, the GP practices will again receive a second material package before the start of the influenza vaccination period. This contains, among other things, the materials needed for the upcoming vaccination recall (customisable postcards and matching envelopes). The intervention is planned to be implemented in the GP practices from 01.07.2022 to 31.03.2024. Figure 1 shows the components of the complex intervention.

**Fig. 1 Fig1:**
[figure not shown]
Components of the complex intervention

### Aims of the study

The main aim of the study is to develop, implement and evaluate a complex intervention to significantly improve vaccination rates for the vaccinations recommended by the STIKO for persons aged 60 and older (seasonal influenza, pneumococci, herpes zoster, COVID-19, and revaccinations against tetanus, diphtheria, and pertussis). The following logic model (Fig. 2) demonstrates how the intervention is intended to work and how it is assumed to affect the intended results according to the MRC framework [26].

**Fig. 2 Fig2:**
[figure not shown]
Logic model of the complex intervention based on Moore et al. (2015)

## Methods and analysis

### Study design

Not only the effect on outcomes (summative evaluation), but also the process of implementing the intervention (formative evaluation) must be examined in order to identify mechanisms of action and contextual factors, as this is a complex intervention [27].

### Summative evaluation

Within the summative evaluation, secondary as well as primary data will be used (see Table 1).

#### Summative evaluation: secondary data

The secondary data analysis is based on data on vaccination rates before and after the intervention, which will be compared between intervention and control group and will address the following research questions:

Does the intervention lead to an increase in influenza vaccination uptake rates in the GP practices among persons insured by one of the six substitute health insurance funds aged 60 and older (primary outcome) group?Does the intervention lead to an increase in the vaccination uptake rate for the other vaccinations recommended by the STIKO for persons aged 60 and older (seasonal influenza, pneumococci, herpes zoster, and revaccinations against tetanus, diphtheria, and pertussis) (secondary outcome)?Since previous analyses of vaccination activity have shown significant regional differences in vaccination uptake rate [28], do the effects in (1) and (2) vary between the participating regions of Westphalia-Lippe, North Rhine and Schleswig-Holstein?

The focus of the summative evaluation will be on a pre-post comparison between the intervention and control group, considering differences between the two groups that already existed before the intervention. For the post analysis, GP claims data from 7 quarters after the start of the intervention are available for analysis (07/01/2022–03/31/2024). Due to the still unknown impact of the COVID-19 pandemic on the next influenza vaccination season, a period of at least 24 months prior to the start of the intervention will be considered for pre-analysis – meaning the vaccination and immunisation uptake rates achieved prior to the intervention. Because influenza vaccination should occur annually, comprehensive information on the baseline population and the number of vaccinated persons is available. The determination of vaccination uptake rates, on the other hand, is more challenging because the size of the population is unclear due to the long periods of time between booster vaccinations. Persons aged 60 and older are recommended to receive a booster vaccination against tetanus, diphtheria, and pertussis only every 10 years. A booster vaccination against pneumococci after 6 years (or later) is beneficial but not generally recommended by the STIKO. Furthermore, there is no recommendation for a booster vaccination against herpes zoster after the basic immunisation has been completed. The available data does not allow to identify if patients aged 60 and older got a booster vaccination against tetanus, diphtheria, and pertussis in the past 10 years and if patients aged older than 60 have already been vaccinated against pneumococci or herpes zoster. Therefore, we will analyse the increase in the vaccination uptake rate among participating GPs compared to non-participating GPs. Provided that the necessary number of cases is achieved, subgroup analyses for individual vaccinations (e.g., pneumococci) are planned.

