### Recruitment

The recruitment of GPs for study participation takes place three months prior to the start of the intervention phase by the three participating regional Associations of Statutory Health Insurance Physicians (ASHIP) Schleswig-Holstein, North Rhine and Westphalia-Lippe, considering the available contingent of participants in their region. In Germany, the ASHIP are bodies under public law, which represent all physicians and psychotherapists treating compulsory insured patients. First, all potentially eligible GPs in the three regions, meaning GPs participating in primary care according to § 73 (1a) SGB V (excluding paediatricians), who have vaccinated patients aged 60 and older insured by the substitute health insurance fund in the past, will be identified. Substitute health insurance funds are a type of health insurance fund with the largest percentage of insured persons on the German market. There are no other major differences between this and other types of health insurance funds. Subsequently, these GPs will be stratified by the three ASHIPs, and randomised into two groups (intervention/control). The potential participating GPs in the intervention group will be contacted by the responsible ASHIP and receive the offer to participate in the intervention group. It is pointed out that participation in the intervention is also associated with participation in the accompanying evaluation study. Subsequently, all enrolled GPs, as well as at least one medical assistant from the practice, complete the online training that is completed after an online knowledge test and submit the certificate of successful participation to the associated ASHIP.

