#### Secondary data

After submitting the certificate and vaccinating at least 20 patients aged 60 and older insured by a substitute health insurance fund in the first quarter of evaluation, the GP will receive an initial starter lump sum payment. Through this lump sum payment, the GP is marked as a participant in the billing data of the ASHIP and is available in a pseudonymised form for the summative evaluation over all quarters considered. Since secondary data (extract of pseudonymised contractual GP billing data according to § 295 SGB V) is used, the relevant data is available for both the intervention and the control group.

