***Summative evaluation (secondary and primary data)***			
**Secondary data**: Extract of pseudonymised contract GP billing data according to § 295 SGB V, n = 2114 GPs (n = 1057 GPs each in the intervention and control group) and at full utilisation ≥ 147,980 patients	**Primary outcome**: Influenza vaccination rate **Secondary outcome**: Vaccination uptake rate of the vaccinations recommended by the STIKO for patients aged 60 and older (except for influenza)	-	Descriptive statistics, pre-post comparison (intervention/control group), cluster analysis, subgroup analyses
**Primary data**: Cross-sectional patient survey in intervention practices (n = 50), pre- and post-implementation (2 x n = 1250 patients), paper & pencil survey	**Secondary outcome**: Vaccine literacy	**Further secondary outcome**: HLS19-VAC-DE subscale of the HLS19 instrument (40)	Descriptive statistics, multivariable regression models, multilevel analysis

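### GPs are randomised before the offer, but the evaluated intervention group is defined by later participation, so the randomised comparison is lost

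*Protocol article*

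**What the plan says.** Under Recruitment, the three ASHIPs first identify every potentially eligible GP. Then "these GPs will be stratified by the three ASHIPs, and randomised into two groups (intervention/control"). Only after that are GPs in the intervention group approached: they "will be contacted by the responsible ASHIP and receive the offer to participate in the intervention group". No such offer is described for controls. Next, "all enrolled GPs, as well as at least one medical assistant from the practice, complete the online training", pass a knowledge test and submit the certificate.

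Under Recruitment, Secondary data, the starter payment, with the patient count taken over the opening evaluation quarter, comes only "After submitting the certificate and vaccinating at least 20 patients aged 60 and older insured by a substitute health insurance fund". The article continues: "Through this lump sum payment, the GP is marked as a participant in the billing data of the ASHIP". The same sentence makes the GP available, pseudonymised, for the summative evaluation. This section also says that billing data exist for both groups.

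Two descriptions of the contrast appear under Summative evaluation: secondary data. The general one is "The focus of the summative evaluation will be on a pre-post comparison between the intervention and control group", taking account of differences that existed beforehand. For the non-influenza vaccinations, after explaining that the population at risk is unknown, the article says "we will analyse the increase in the vaccination uptake rate among participating GPs compared to non-participating GPs".

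Table 1 gives the analysed size as "n = 2114 GPs (n = 1057 GPs each in the intervention and control group").

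**The concern.** Randomising before consent, with routine data on everyone, gives a clean comparison of GPs assigned to the offer with GPs assigned to control. That comparison holds only if each GP is analysed in the assigned group. Here the intervention group is formed by acts after randomisation: accepting, training, certifying and reaching a vaccination count. The last is itself vaccination activity, close to the outcome, and no matching condition is described for controls.

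GPs who volunteer for a paid vaccination programme and quickly reach the count may well be on a different trajectory from GPs in general. If so, the contrast mixes the intervention effect with self-selection. The Discussion says the results will inform a decision on including the intervention in standard care, so the basis of the effect estimate matters.

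**Working it through.** **1. Who is in the intervention group.**

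- Recruitment: assignment comes first, the offer second.
- Secondary data (under Recruitment): entry to the evaluation as a participant follows the payment, not the assignment.
- Primary data: the patient-survey practices are drawn from 1057 GPs of the intervention group, and the online survey goes to all intervention practices, again 1057. The figure therefore appears to count enrolled GPs, not GPs assigned to the offer.
- Sample: the full 3% effect is carried through. The 7% reserve is described only as securing case numbers, and no allowance is made for refusal.

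No section states an analysis by assignment or places GPs who decline or miss the threshold.

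**2. The plan's own figures.** Inputs from Sample: 17,508 patients before clustering, ICC 0.08, 90% power, two-sided 5%, effect 3% (read here as percentage points), cluster sizes 48 and 28.

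- Primary outcome: design effect 1 + 47 × 0.08 = 4.76; 17,508 × 4.76 = 83,338; 83,338 / 48 = 1736 GPs; 868 per group.
- Secondary outcome: 1 + 27 × 0.08 = 3.16; 17,508 × 3.16 = 55,325; 55,325 / 28 = 1976; 988 per group; 988 × 1.07 = 1057.

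The cluster steps reproduce. The 17,508 is taken as given. A standard two-proportion formula for an absolute 3-point rise gives at most 2 × 5836 = 11,672, but that is a separate matter.

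**3. False-positive rate under a differential trend.** The standard error implied by 868 per group is 3 / (1.960 + 1.282) = 0.925 points. At 1057 it is 0.925 × √(868/1057) = 0.839. If there is no true effect and participants' rates would rise anyway by b points more than controls' (assumed), then

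P(reject) = 1 − Φ(1.960 − b/SE) + Φ(−1.960 − b/SE).

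| b (points, assumed) | 868 per group | 1057 per group |
|---|---|---|
| 0.5 | 8% | 9% |
| 1.0 | 19% | 22% |
| 1.5 | 37% | 43% |
| 2.0 | 58% | 66% |

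**4. Cost of analysing as randomised.** Let f be the share of offered GPs who take part. The article does not give it, so a range is shown. If non-participants show no effect, the as-randomised effect is 3f points. GPs needed per randomised group are 868/f² (primary) or 988/f² (secondary). Primary-outcome power with n randomised per group is Φ(3.242 × f × √(n/868) − 1.960).

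| f (assumed) | Effect (points) | GPs per group for 90%, primary / secondary | Power, primary, n = 1057 |
|---|---|---|---|
| 0.90 | 2.70 | 1072 / 1220 | 90% |
| 0.75 | 2.25 | 1543 / 1756 | 77% |
| 0.50 | 1.50 | 3472 / 3952 | 43% |
| 0.25 | 0.75 | 13,888 / 15,808 | 14% |

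If 1057 instead counts enrolled participants, the offer group is 1057/f. At f = 0.50 that is 2114. With as many controls, 3.242 × 0.50 × √(2114/868) − 1.960 = 0.57, so power is about 72%.

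**The case against.** Four points on the other side carry weight.

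- *Scope of the quoted sentence.* It follows from the denominator problem for the tetanus, diphtheria, pertussis, pneumococcal and zoster vaccinations, so literally it covers the secondary outcome. A reader might infer that the article states the same contrast for influenza. It does not: there it says intervention versus control group. The point reaches the primary outcome only through the payment marker.
- *Baseline adjustment.* The plan uses at least 24 months of earlier data and considers existing differences. A reader might take the between-practice SD of levels, √(0.473 × 0.527 × 0.08) = 0.141, and argue that a gap of 0.2 SD, or 2.8 points, would mimic the whole target. That does not fit the planned analysis. Stable level differences can be removed, and the article gives no SD for change. Only differential change remains, which is why smaller assumed drifts are used above.
- *Placement of decliners.* A reader might infer that GPs who refuse are moved into the comparator, or dropped. Neither is stated. The term non-participating may simply mean randomised controls.
- *Level of detail.* Analysis populations are often defined in an SAP, which is not shown, and the Abstract calls the design controlled rather than randomised. But the article itself fixes both the contrast and the marker that identifies the group. If the extract flags only paid participants, a later SAP may be unable to recover the GPs assigned to the offer.

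A reader might also fault the choice of equal groups of 1057 as wasting control data. That is an efficiency preference, and the article gives no number of eligible GPs from which to size any gain.

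**Conclusion.** The concern holds. As written, the plan gives up the randomised comparison: explicitly for the non-influenza vaccinations, and through the payment marker for influenza as well. The 20-patient condition aggravates this, because it selects one group only, after randomisation, on something close to the outcome.

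The size of any bias cannot be derived from the article. As an illustration, a 1-point differential trend raises the false-positive rate from 5% to about 19% (868 per group) or 22% (1057 per group). This assumes the drift and takes the precision implied by the article's own sample-size calculation. If 17,508 exceeds what an absolute 3-point effect requires, true precision would be better, the false-positive rates higher and the dilution losses smaller.

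**What to change.** - Carry the randomised assignment of every GP into the billing extract.
- For both claims-data outcomes, make the primary comparison all GPs randomised to the offer versus all GPs randomised to control, whether or not they accept, train or reach the threshold.
- Report the effect in participants as a complier-average effect with the randomised offer as instrument. Define participation with care: a GP who trained but missed the 20-patient count was still exposed.
- Define non-participating. Label any participant-versus-non-participant contrast as observational, and keep decliners out of its comparator.
- Restate power or the detectable effect with an assumed participation share, and say whether 1057 counts randomised or enrolled GPs.

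The cost is revised wording and an extract that includes assigned GPs who did not take part. The article says billing data exist for both groups, but not whether decliners can be linked to their assignment in pseudonymised form; this needs confirming. The real downside is dilution, as tabulated. At low acceptance the as-randomised analysis may be underpowered, and the article does not say how many GPs are randomised.
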